#### Improving adherence

If participants do not log in to the training website for 10 days, they will automatically receive a reminder email asking them whether they are experiencing any problems with the program. Responses will be handled by the research team individually. In addition to the 1 day of experience sampling that will take place each week, in the questionnaires we will also include suggestions for exercises provided in the respective week of the training program.

### Assessments

Assessments in the study will include (1) outcome assessments, (2) process assessments, (3) smartphone sensing, and (4) behavioral and self-reported compliance on the training website. Table 1 provides an overview of all assessments. In the following section, we describe the different types of assessments.

**Table 1 Tab1:** Measures

	Pretest	ESM	Post-Test	Follow-Up
Intake				
Demographics	X			
Main Outcome Assessment				
Work-related Perseverative Thinking	X	X	X	X
Secondary and Process Outcome Assessment				
Recovery Experience Questionnaire [62]	X	X	X	X
State of Being Recovered [63]	X	X	X	X
Positive Work Reflection [64]	X	X	X	X
Three‐Dimensional Work Fatigue Inventory [65]	X	X	X	X
Standardized Sleep Inventory [66]	X	X	X	X
Life Engagement [adapted from 67]	X	X	X	X
Multidimensional Mood Questionnaire [68]	X	X	X	X
Multidimensional State Mindfulness [69]		X		
Five Facet Mindfulness Questionnaire [70]	X		X	X
Negative Activation [based on 71]	X	X	X	X
Perceived Stress Scale (German version) [72]	X	X	X	X
Affect Regulation [based on 73]	X	X	X	X
Further Outcome and Control Variables				
Big Five Inventory [74]	X			
Trait Self-Control [75]	X			
Utrecht Work Engagement Scale [76]	X	X		
Appreciation at Work [77]	X	X		
Emotional Resources [78]	X	X		
Autonomy [79]	X	X		
Emotional Demands [80]	X	X		
Home Demands (self-made)	X	X		
Home Resources (self-made)	X	X		
Self-Control Demands [81]	X	X		
Unfinished Tasks [32]	X	X		
Interoception [82]	X	X		
Data Quality (self-made)		X	X	X
Situational Questions		X		

#### Outcome assessments

We will evaluate the effectiveness of both interventions by comparing the respective levels of the outcome variables at pretest, posttest, and a 3-month follow-up. The pretest will take place before the first week of experience sampling and the intervention. The posttest will take place in the week after the intervention. The follow-up will take place 3 months after the posttest to evaluate whether changes in work-related PT remained stable over this more extended period or reverted to their pre-intervention levels. We will ask the participants to evaluate all primary and secondary outcomes using a time frame of 2 weeks.

The primary outcome in these pretest, posttest, and follow-up assessments is *work-related PT*. We will measure work-related PT using a combination of three worry items [60], four rumination items [28], and two brooding/rehearsal items [61]. Items have been adapted to the work context. The response scale ranges from 1 (not true at all) to 5 (very true). For a complete list of items, see the supplementary online materials on the OSF: https://osf.io/jzt6g/. This group of items has not been used in this combination as an indicator of PT before. We therefore evaluated the measure in terms of model fit and convergent and discriminant validity in a sample of 202 employees working at least part-time. A unidimensional model fit the data well (CFI = 0.98; TLI = 0.97; RMSEA = 0.07; SRMR = 0.03), and the pattern of correlations with (a) measures of similar constructs, such as affective rumination [35], detachment [62], and (b) relevant correlates (e.g., emotional demands, fatigue, stress, and affect) was meaningful and as expected. The internal consistency of the scale was good: McDonald’s ω = 92.

Secondary outcomes will be the following work and mental health variables, which are conceptually and typically empirically associated with work-related PT.

*Detachment*. We will measure psychological detachment with a four-item subscale from the Recovery Experience Questionnaire [62]. The rating scale ranges from 1 (not true at all) to 7 (very true).

*State of being recovered.* State of being recovered will be measured with four items proposed by Sonnentag and Kruel [63]. On the pretest, posttest, and follow-up questionnaires, we will ask the participants how rested and refreshed they felt during the last 2 weeks using a 5-point scale ranging from 1 (not true at all) to 5 (very true).

*Fatigue*. We will assess fatigue using nine items from the German version of the Three-Dimensional Work Fatigue Inventory [65]. This instrument differentiates between physical, mental, and emotional work fatigue with parallel items assessing tiredness and reduced functional capacity. We will ask participants to rate their fatigue using a 6-point scale ranging from 1 (never) to 6 (always).

*Sleep quality.* Sleep quality will be assessed with the sleep quality subscale from the Standardized Sleep Inventory [66]. Participants will be asked to rate their sleep with three adjectives (good, undisturbed, ample) ranging from 1 (never) to 7 (always).

*Affective well-being*. We will operationalize affective well-being in terms of good mood and (low) tense arousal with four items taken from the Multidimensional Mood Questionnaire [68]. Participants will rate their mood using adjectives such as pleasant, content, tense, or nervous on a 7-point scale ranging from 1 (not at all) to 7 (very much so).

*Negative activation.* Negative activation will be measured with five adjectives that are based on the 12-point circumplex core-affect model [71]. Adjectives include affective attributes such as irritated, upset, or agitated. We will apply the same 7-point scale as already used for the measurement of affective well-being ranging from 1 (not at all) to 7 (very much so).

*Stress.* Stress perceptions will be assessed with a 4-item German version of the Perceived Stress Scale [72]. The stress items will be answered on a 5-point Likert scale ranging from 0 (never) to 5 (very often). We will use the overall score as an indicator of the individual stress level.

Also, the pretest, posttest, and follow-up assessments will include several other variables, such as personal and work characteristics. Table 1 presents all constructs, and further details are provided in the Codebook on the OSF at https://osf.io/jzt6g/.

#### Process assessment

The measurement burst design will include various phases of intensive longitudinal assessments. In Phases 2, 4, and 5, participants will receive links to self-reports four times per day from Monday morning through Saturday morning. We will prompt participants in the morning, directly after work, at 8 pm, and before bedtime. The assessments will include items on work-related variables (e.g., job demands and resources, work engagement), mental health variables (e.g., fatigue, sleep quality, stress, recovery), and personal characteristics (e.g., affect regulation, negative activation, personal resources, and working hours). All items refer to the state aspects of the constructs. Table 1 presents the measures, and the project's Codebook on the OSF repository offers more details.

During the 6 weeks of the intervention, we will implement 1 day of experience sampling each week with a total of five assessments (beginning on Tuesday at bedtime followed by four assessments on Wednesday). The measurements will parallel those in Phases 2, 4, and 5.

#### Smartphone sensing

We will acquire sensor data from participants' mobile phones. While participants fill out the daily questionnaires, we will obtain data for the acceleration and orientation of the device. These passive sensor data may provide incremental information about individuals' internal states such as arousal or fatigue [83] and serve as a proxy for data quality. Hence, the use of additional sensor-based assessments will establish a multimethod assessment approach.

#### Behavioral and self-reported engagement

A key discrepancy between face-to-face interventions and digital self-help eHealth/mHealth training programs is the absence of scheduled appointments. This lack of social interaction requires participants to plan their own intervention schedule, complete the exercises conscientiously, and identify which content areas need to be reiterated. Failure to do so (e.g., due to low commitment) might ultimately lead to attrition [84].

Although researchers tend to agree that engagement plays a significant role in the effectiveness of self-help interventions, the determinants of compliance in eHealth/mHealth and its effects on effectiveness are largely unexplored [85]. Nevertheless, differences in engagement may partly explain the heterogeneity in effect sizes found for interventions that are comparable to each other in terms of content, delivery format, duration, dosage, and target population. Therefore, we will repeatedly assess participants’ behavioral adherence throughout the training period on the dimensions of frequency, intensity, time, and type [85].

### Data analyses

Our research goals refer to different levels of the data. Besides evaluations of the interventions’ efficacy, one part of our research involves hypotheses on the within-day level. By contrast, others focus on the same processes between days and several weeks. We will address the complexity of our data by applying various statistical approaches.

To evaluate changes across time in primary and secondary outcomes, we will use the pretest, posttest, and follow-up measures. These measures represent indicators of latent variables estimated separately in the two experimental groups and the two waitlist control groups combined. Using the latent variables (latent states), we will set up Multigroup Latent Change Models (with baseline-change and neighbor-change variants). Latent Change Scores from (a) pretest to posttest and from pretest to follow-up (baseline-change) and (b) from pretest to posttest and from posttest to follow-up (neighbor-change) will provide information about the effect sizes from pre to post and on the maintenance of the effects from posttest to follow-up [86]. To estimate the models, we will use the Bayes estimator as implemented in Mplus [87]. We will determine the convergence diagnostic [88], evaluate potential convergence issues by doubling the number of iterations, and visually inspect histograms for all parameters and the trace plots for the Markov chains. For the difference between the pre-post change scores in both experimental groups, we will set up an informative prior with a normal distribution, a mean of zero, and a small variance, that is, *N*(0, 0.010). This prior corresponds to the assumption that the change scores in the two groups should be equal, implying similar efficacy between the two interventions. A small variance around the mean of the prior will reflect our confidence that the difference between the change scores will be minimal but will allow for small differences [89]. This distribution implies that 95% of the standardized differences in the means ranges from -0.2 and 0.2. Accordingly, the efficacy of the two interventions will be considered equal if the standardized difference in the latent change scores based on the posterior distribution lies within a range of -0.2 and 0.2.

We will use the assessments paralleling the interventions to estimate a Growth Model separately in each group. To account for potential nonlinear growth over time, we will implement free time scores when estimating the slope growth factor in each group. The time score in the first week will be fixed to zero (centering point), whereas the time score in the sixth week will be fixed to one. Hence, the mean of the slope growth factor will represent the average rate of change from Week 1 to Week 6.

The Dynamic Structural Equation Modeling (DSEM) [90] approach will be applied to the measurement burst part of the study. DSEM is suitable for addressing the particular issues of (a) intensive longitudinal data, (b) autoregressive and cross-lagged within-person effects, and (c) different time-lags (between and within persons). DSEM combines four modeling techniques: multilevel modeling, time-series modeling, structural equation modeling, and time-varying effects modeling. The multilevel part of DSEM will allow us to model the correlations that are due to individual-specific effects. The time-series part of DSEM will enable us to model the correlations that are due to the proximity of observations. The structural equation modeling part will be based on correlations between different variables. The time-varying effects modeling will be based on correlations that are due to the same stage of development. This flexibility makes DSEM suitable for testing the hypotheses in our study. The postulated mediation and moderation effects will apply to the within-day level (Level 1) of analysis. To test the time course of the processes, job stressors will be measured directly after work. Negative activation, detachment, and work-related PT will be measured in the evenings. Strain variables and the state of being recovered will be assessed in the mornings. This procedure will allow us to test for autoregressive and cross-lagged associations between the constructs. Recovery strategies, mindfulness, and emotion regulation are also Level 1 variables and can be accounted for in the DSEM. Hypotheses focusing on the interventions’ effectiveness at a daily level can be implemented as a cross-level predictor. Moreover, given that the study will manipulate work-related PT, changes in the intercepts, variances, and covariances of the variables are expected and will be modeled as random effects.

In addition, the DSEM framework can account for a more realistic implementation of the time variable within a continuous-time modeling approach. This aspect of the model can account for the assumptions that the same processes will occur at the microlevel (i.e., within days) and the macrolevel (i.e., between weeks). Given that in intensive longitudinal data, uneven individual observations are most likely to occur, the analyses need to be able to account for the different time lags. Using the DSEM approach, we can examine the associations of interest by using parameters that are not biased by a violation of the assumption of equal time intervals.

For all analyses, we will use the statistical modeling programs Mplus [87] and R [91].

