## Methods/design

### Study design

In this protocol, we describe a four-armed randomized controlled trial with measurement bursts (i.e., periods of intensive longitudinal data collection) conducted to compare the efficacy of two 6-week online interventions for recovery from work. We will randomly assign the participants to one of four conditions: (a) experimental condition 1: CBT-based techniques, (b) experimental condition 2: mindfulness-based techniques, (c) waitlist condition 1: CBT-based techniques, (d) waitlist condition 2: mindfulness-based techniques. To monitor progress for the assessments, we will maintain a parallel structure for all four groups, meaning that the waitlist control groups will respond to the same questionnaires in all phases of the study. We will invite all participants via email to complete the pretest (Phase 1) and the first measurement burst (comprising four daily assessments from Monday through Friday plus one assessment on Saturday morning). This first week of intensive assessments represents Phase 2. After Phase 2, participants in the experimental groups will immediately receive access to the online interventions. During the 6 weeks of the interventions in both experimental groups, participants in all groups will be prompted once a week to provide 1 day of experience-sampling measures (four daily assessments, Phase 3). Approximately 7 weeks after Phase 2, participants will begin the second week of intensive longitudinal assessments (similar to Phase 2) followed by the posttest (Phase 4). Following Phase 4, individuals in the waitlist control groups will receive access to the online training programs in either the CBT-based or mindfulness-based form—depending on their allocation at the start of the study. Finally, Phase 5 will take place 3 months after the end of Phase 4 and will again include 1 week of intensive longitudinal assessments and a follow-up assessment (similar to Phase 4).

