### Participants and recruitment

The study will be conducted with employed volunteers recruited through newspapers, flyers, and social media. To estimate the power to detect an assumed meta-analytical pre-post effect of *d* = 0.36 [42], if such an effect exists in the population, we ran a Monte Carlo simulation. Our analyses for the primary outcome involve a Latent Change Model (see below for more details). The simulations showed that for a two-tailed test with 90% power and a priori alpha level of 5%, we would need *N* = 136 participants in each experimental group to be able to detect a pre-post difference of approximately *d* = 0.35 (in our case represented by the intercept of the latent change factor) if it exists in the population.

In addition, for the analyses of the dynamic associations with the measurement bursts, previous studies have shown that the power to detect a relatively small standardized indirect effect of 0.1 was = 0.81 for ICC ≥ 0.10 with *J* ≥ 100 clusters with a within-cluster sample size of *n *_*j*_ = 20 [56]. Because our research questions refer in part to the upper levels of the hierarchical data, we will need a sample size that will allow us to estimate unbiased parameters for the mediation models at the person-level of analysis as well. Li and Beretvas [57] showed that a multilevel SEM required at least 80 clusters to circumvent convergence issues.

Considering all the analyses' requirements and assuming a drop-out rate of up to 20% after Phase 3 and up to an additional 20% after Phase 4, we aim to recruit 600 participants (i.e., 480 in Phase 4 and 384 in Phase 5). The analyses will be conducted using all available data (either with Full Information Maximum Likelihood or Bayesian estimation). To be eligible for this study, participants must (1) be 18 years or older, (2) be working regular working hours (no shift work) at least part-time, (3) not be in psychotherapeutic or psychiatric treatment, and (4) be smartphone users with mobile internet access. In addition, participants must be able to read and write in German.

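### The efficacy model leaves out the experience-sampling PT scores that could inform a missing posttest, so participants lost before posttest are handled as missing at random given pretest and group only

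*Protocol article*

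**What the plan says.** **Efficacy model (protocol article, Data analyses).** "To evaluate changes across time in primary and secondary outcomes, we will use the pretest, posttest, and follow-up measures". These measures are the indicators of latent states, "estimated separately in the two experimental groups and the two waitlist control groups combined", in a multigroup latent change model. On the estimator: "To estimate the models, we will use the Bayes estimator as implemented in Mplus".

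**Expected loss (Participants and recruitment).** The target is set "assuming a drop-out rate of up to 20% after Phase 3 and up to an additional 20% after Phase 4", and the article concludes: "we aim to recruit 600 participants (i.e., 480 in Phase 4 and 384 in Phase 5").

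**Missing data (same section).** "The analyses will be conducted using all available data (either with Full Information Maximum Likelihood or Bayesian estimation").

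**What else is collected.** Table 1 marks work-related PT under ESM as well as at the three waves. Under Study design, during the six training weeks, "participants in all groups will be prompted once a week to provide 1 day of experience-sampling measures". Process assessment gives the weekly days the same content as the bursts of Phases 2, 4 and 5. The Phase 4 burst comes before the posttest.

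**Where those data go (Data analyses).** The weekly data feed a growth model fitted separately in each group. The bursts feed dynamic structural equation models. The article does not link either to the latent change model.

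**The concern.** Likelihood and Bayesian estimation ignore a missing posttest correctly only if missingness is random given the variables in the model. For someone who leaves during training and does not return, those variables are the pretest and the group. The estimate then assumes that, at a given pretest score, leavers would have ended where stayers of the same group ended.

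The ESM scores show how a leaver's PT was developing before leaving, and the efficacy model does not see them. In a self-guided online training it is plausible that leaving is related to response. The section on engagement expects low commitment to lead to attrition. Waitlist members have no training to abandon and receive access only after Phase 4, so equal dropout mechanisms across arms cannot be presumed.

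At stake is the primary pre-post effect, planned around d = 0.36. If the mechanism differs between the two trainings, the comparison judged against a range of -0.2 to 0.2 is affected as well.

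**Working it through.** **1. The plan's own figures.** 600 x 0.80 = 480 at Phase 4, and 480 x 0.80 = 384 at Phase 5. Both reproduce. Two thirds of participants go to the trainings. With an equal split between them (assumed), each training has about 200 and the combined waitlists about 200. At 20% loss, about 40 of each 200 have no posttest and 160 do.

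**2. Method.** One training arm, PT in SD units, with pretest, last weekly PT and posttest trivariate normal and a true change of -0.36. Twenty percent leave before posttest, by a logistic model. With a and b fitted in completers and averaged over everyone randomised:
- pretest only: change = mean(a + b x pre) - mean(pre)
- with weekly PT: change = mean(a + b x pre + c x weekly) - mean(pre)

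For this dropout pattern these equal the large-sample likelihood estimate without and with the auxiliary variable. Loss in the waitlist is taken as random, so an error in the arm passes in full into the contrast. The correlations and odds ratios (OR) are assumptions, because the article gives none.

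**3. Leaving depends on weekly PT change since pretest; poor responders leave.** 1,000,000 persons per scenario; pretest-weekly correlation 0.5 (first two rows) or 0.6 (last two).

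| r pre-post | r weekly-post | OR 1.5, pretest only | OR 2, pretest only | OR 3, pretest only | Weekly PT added (all three ORs) |
|---|---|---|---|---|---|
| 0.5 | 0.6 | -0.388 | -0.406 | -0.425 | -0.358 to -0.361 |
| 0.5 | 0.7 | -0.397 | -0.419 | -0.449 | -0.360 to -0.363 |
| 0.6 | 0.7 | -0.390 | -0.412 | -0.432 | -0.359 to -0.362 |
| 0.6 | 0.8 | -0.398 | -0.423 | -0.454 | -0.359 to -0.360 |

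At OR 1 both models give -0.358 to -0.362, so there is no bias.

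**4. Leaving depends on weekly PT given pretest.**
- Weekly-post r 0.7 to 0.8, pretest only: -0.39 to -0.40 (OR 1.5), -0.42 to -0.43 (OR 2), -0.44 to -0.46 (OR 3).
- Weekly-post r 0.5 with pre-post r 0.6, pretest only: -0.377, -0.385 and -0.398 at the same ORs.

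The smallest bias is 0.377 - 0.360 = 0.017 and the largest 0.46 - 0.36 = 0.10. The range is therefore about 0.02 to 0.10 SD, or 6% to 28% of 0.36.

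**5. Direction reversed.** If improved participants leave (OR 2, r 0.6 and 0.7), the pretest-only estimate is -0.302. The effect is understated by 0.360 - 0.302 = 0.058 SD.

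**6. Leaving depends on posttest-level PT given pretest (OR 2; pretest-weekly r 0.55).**

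| r pre-post | r weekly-post | Pretest only | Weekly PT added | Bias before and after | Share removed |
|---|---|---|---|---|---|
| 0.6 | 0.8 | -0.463 | -0.413 | 0.103, 0.053 | 0.050/0.103 = 49% |
| 0.5 | 0.7 | -0.469 | -0.433 | 0.109, 0.073 | 0.036/0.109 = 33% |
| 0.6 | 0.6 | -0.459 | -0.444 | 0.099, 0.084 | 0.015/0.099 = 15% |

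With weaker weekly-post correlations the share falls to about 5%.

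**7. Size against precision.** With 160 completers per group, the standard error of the adjusted group difference is sqrt(2(1 - r^2)/160): 0.097 at r = 0.5 and 0.089 at r = 0.6.

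**The case against.** **A condensed article may leave auxiliary variables to the full analysis plan.** This is fair in part. The article neither lists nor excludes them, and if the full plan already includes them the point falls away. But the article does state the model's indicators, its grouping, its estimator and its handling of missing data. The point concerns that stated choice.

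**The promise to use all available data might seem to cover the ESM scores.** It does not. These estimators use only the variables in the model, and the article names the three waves.

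**A reader might infer that every leaver is handled from the pretest alone.** That holds only for those who never return. Someone who misses the posttest but comes back in Phase 5 contributes follow-up data. Stopping training is also not the same as skipping the posttest, which is paid separately and runs in parallel in all groups.

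**A reader might infer that the effect will be overstated.** The documents do not support this. They tie attrition to commitment and self-planning, not to high PT. The direction is an assumption, and step 5 shows the reverse. Similar loss in the waitlist would partly cancel in the between-group contrast, though not in the within-arm change.

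**A reader might infer that adding weekly PT removes the bias.** In steps 3 and 4 this follows from the set-up, because leaving was generated from the score then added. Step 6 shows only partial removal. Weekly PT is also a state measure from one sampling day a week, not the nine-item two-week scale, and early leavers have little of it.

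**The bias is at most about one standard error.** True under these inputs. Unlike sampling error, however, it does not shrink with more participants, and it can be reduced at little cost.

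**Conclusion.** The point holds as a conditional weakness with a cheap remedy, not as an error in the plan. For participants lost permanently before posttest, the efficacy model rests on missingness being random given pretest and group, although PT data bearing on the missing value are collected.

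If leaving depends on PT during training, the within-arm change is biased, and the contrast with the waitlist is biased as far as the mechanisms differ. The size is about 0.02 to 0.10 SD on a true 0.36, in either direction. This rests on assumed inputs: 20% loss, OR 1.5 to 3 per SD, pre-post r 0.5 to 0.6, weekly-post r 0.5 to 0.8, and random loss in the waitlist. If leaving is unrelated to response, there is no bias.

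Using the ESM scores corrects the bias fully only where leaving depends on those observed scores. Where it depends on posttest-level PT, about 5% to 50% is removed. Label: cheap improvement.

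**What to change.** Keep the three-wave PT scale as the sole outcome. In every group of the latent change model, add the person-level ESM PT scores as auxiliary variables correlated with the latent states: the Phase 2 mean, the available Phase 3 weekly means, and the Phase 4 burst mean. Alternatively, use them as predictors in a multiple-imputation step before the model. Do the same for secondary outcomes that have an ESM counterpart. Fix the choice before outcome data are examined.

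State the limit alongside it: the assumption becomes weaker, but missingness that depends on unobserved PT is corrected only in part, and little is gained for those who leave before the first weekly day.

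Cost: a change of analysis wording and a larger model with more parameters and possibly slower convergence. It needs no new data, visits or participants.

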### Procedure

The overall procedure is shown in Fig. 1. The study will combine a longitudinal design with three experience-sampling phases (measurement bursts). After completing the pretest (Phase 1), participants will begin the first 5 days of the experience sampling (Phase 2). In this week, we will assess all work-related and personal variables in daily life (for an overview of all variables, see section on assessments below). During the experience-sampling phases, participants will be prompted once each morning, once in the (late) afternoon, once during the evening, and once directly before going to sleep. The morning and afternoon sessions will take approximately 2 min, whereas the evening and night sessions will take about 5 min each.

Following Phase 2, participants in the intervention groups will begin with either the CBT-based training or the mindfulness-based training. Because both interventions will last for 6 weeks, we will implement the contents of the interventions in both groups sequentially. Both training programs can be considered low-dose interventions [42]. Based on the literature, we do not expect training-related harms or adverse events. However, the study will monitor such adverse effects, and the participants may contact the research team via email at any time during the study.

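### The two waitlist groups stay combined in the model at follow-up, after they have been given two different trainings; the pretest-posttest comparison is sound, but change scores involving follow-up have no untrained control

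*Protocol article*

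**What the plan says.** The outcome model uses three waves: "To evaluate changes across time in primary and secondary outcomes, we will use the pretest, posttest, and follow-up measures" (Data analyses). The grouping follows in the next sentence: "These measures represent indicators of latent variables estimated separately in the two experimental groups and the two waitlist control groups combined". That makes three groups, and the article gives no other grouping for any wave. The model defines change from pretest to posttest, from pretest to follow-up and from posttest to follow-up. The same section ties effect sizes to the pre-post change and ties the step from posttest to follow-up to maintenance.

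On timing, the Study design section states: "Following Phase 4, individuals in the waitlist control groups will receive access to the online training programs in either the CBT-based or mindfulness-based form", according to the allocation made at the start. It adds that "Phase 5 will take place 3 months after the end of Phase 4". The Procedure section gives the length of training: "Because both interventions will last for 6 weeks". The waitlist groups answer the same questionnaires as the others in every phase, so they have follow-up data.

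Outcome assessments gives the purpose of the follow-up as "to evaluate whether changes in work-related PT remained stable over this more extended period" or went back to pre-intervention levels. The opening sentence of that section is broader. It says that effectiveness will be evaluated by comparing outcome levels at pretest, posttest and follow-up. The Methods part of the abstract states the primary expectation as a reduction relative to the waitlist groups.

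**The concern.** Combining the two waitlist groups is justified while both are untreated. Until posttest they differ only in which program they will later receive. After posttest one is offered the CBT-based training and the other the mindfulness-based training. The group that carries the control label at follow-up is therefore a mixture of two offered trainings.

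Two things are at stake. First, anyone who reads the model's pretest-to-follow-up change scores across groups would be comparing earlier with later training, and a lasting benefit could look lost. Second, the follow-up mean of the combined waitlist describes neither program, in a trial whose aim is to compare the two.

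**Working it through.** **1. The plan's own figures.** Participants and recruitment assumes 20% dropout after Phase 3 and a further 20% after Phase 4, from 600 recruited: 600 × 0.8 = 480 at posttest and 480 × 0.8 = 384 at follow-up. Both reproduce exactly. The 136 per experimental group comes from a simulation whose inputs are not all given. It concerns the pre-post difference, and nothing below depends on it.

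**2. Training status by wave.** Three months is about 13 weeks and training lasts 6. A waitlist participant who starts at once is therefore about 13 − 6 = 7 weeks past training at follow-up.

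| Wave | Experimental arms | Waitlist, CBT | Waitlist, mindfulness |
|---|---|---|---|
| Pretest | untrained | untrained | untrained |
| Posttest | trained | untrained | untrained |
| Follow-up | trained | offered CBT training | offered mindfulness training |

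Pooling the last two columns is sound in the first two rows and not in the third. At follow-up, 0 of the 384 expected participants belong to a group that is untrained by design.

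**3. Group sizes at follow-up (assuming equal dropout).** With two thirds allocated to the experimental conditions, each experimental arm starts with 600 × 2/3 ÷ 2 = 200 and has 200 × 0.64 = 128 at follow-up. The combined waitlist also has 200 × 0.64 = 128, that is 64 + 64. The article also speaks of an equal distribution into all four groups. Under that reading an experimental arm has 150 × 0.64 = 96 and the combined waitlist has 300 × 0.64 = 192 (96 + 96). The precision of the contrast is the same: 1/128 + 1/128 = 1/96 + 1/192 = 1/64.

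**4. Size of a pretest-to-follow-up contrast with the combined waitlist.** Let the experimental arms keep d = 0.36 in full, and let the waitlist gain a share f of that effect. The contrast is 0.36 × (1 − f). For illustration, take a simple two-group comparison with SD 1 and two-sided alpha 5%. Power is then approximately Φ(contrast × √64 − 1.96). For f = 0 this is Φ(2.88 − 1.96) = Φ(0.92) = 82%.

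| Share f gained by the waitlist | Contrast | Approximate power |
|---|---|---|
| 0 | 0.36 | 82% |
| 25% | 0.27 | 58% |
| 50% | 0.18 | 30% |
| 75% | 0.09 | 11% |
| 100% | 0 | 5% (the alpha level) |

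The article gives no figure for f, so the whole range is shown.

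**5. Posttest to follow-up.** Under the same assumptions the experimental arms change by 0 and the waitlist improves by 0.36 × f. That improvement would be a real training effect. It misleads only if it is taken for drift in an untreated control group.

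**6. Mixing two programs.** If the trainings are equally effective, pooling leaves the waitlist mean undistorted. If they differ, for example 0.46 and 0.26 (assumed), the combined waitlist averages (0.46 + 0.26)/2 = 0.36. The follow-up contrasts become 0.46 − 0.36 = +0.10 and 0.26 − 0.36 = −0.10. Neither is the effect of a training against no training.

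**The case against.** The strongest reply is that the article never announces an experimental-versus-waitlist test at follow-up. Data analyses ties effect sizes to the pre-post change and uses follow-up for maintenance, and asking whether a change stayed or reverted is a within-arm question. The one between-group contrast spelled out there is CBT-based against mindfulness-based training on pre-post change. The latent variables are estimated separately by group and no constraint involving the waitlist is described, so its follow-up mean need not disturb the experimental arms' estimates. This stands, and it limits the point. It does not remove it, because the written grouping covers all three waves, nothing restricts the waitlist to the first two, and the opening of Outcome assessments invites a comparison of levels at follow-up.

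A reader might infer that the primary result is biased. The documents do not support that: the hypothesis concerns work-related perseverative thinking after the intervention, the sample size is set for a pre-post difference, and both waitlist groups are untreated until after posttest.

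A reader might also infer that the follow-up contrast will be 0 instead of 0.36. That is the extreme case of full uptake, equal efficacy and full maintenance. Waitlist participants receive access, and how much they use it is up to them.

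Finally, the lack of an untreated control for maintenance comes from the waitlist design, which the article discloses, and regrouping does not cure it. A condensed article may also leave the list of contrasts to a fuller plan. The grouping, however, is stated here and does not fit the third wave.

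**Conclusion.** The point holds for the change scores that involve follow-up, and only for them. One grouping is fixed for three waves, but the combined waitlist is an untreated control at the first two only. The pretest-posttest comparison, and pooling the waitlists for it, is sound.

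Any pretest-to-follow-up contrast with the combined waitlist would compare immediate with delayed training. It would lie between 0.36 and 0, depending on how much the waitlist gains, provided the experimental arms maintain the assumed effect. Harm from mixing the two programs arises only if they differ in efficacy.

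It would go too far to say that only CBT-based against mindfulness-based training remains randomised at follow-up. Immediate against delayed training is still a randomised comparison; it is just not trained against untrained. Maintenance within an experimental arm has no untreated control, so it is open to time trends, regression to the mean and the further dropout of up to 20% after Phase 4.

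**What to change.** In Data analyses, state that the combined waitlist serves as the untreated control for pretest-posttest only. For the follow-up wave, model the two waitlist groups separately by allocated program, as delayed-treatment groups. One way is a four-group model in which the waitlist groups share their pretest and posttest parameters and have their own follow-up parameters. Their change from posttest to follow-up then shows how each program performs when given later.

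Describe maintenance in the experimental arms as a within-arm estimate without an untreated control. Name CBT-based against mindfulness-based training as the interpretable randomised comparison of programs at follow-up. If immediate against delayed training is reported, label it as such. Align the opening sentence of Outcome assessments with this.

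No new data or design change is needed. The cost is smaller waitlist groups at one wave (about 64 each, or 96 each under equal four-way allocation) and a more modest follow-up claim. The change should be written down before the follow-up data are analysed, because a later regrouping would look driven by the results.
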